## 8. Criteria for Evaluation

### 8.1. Primary Efficacy Endpoint

The co-primary endpoints are the sensitivity and specificity of IDx-DR with the RV700 detecting more than mild DR (mtmDR) based on eye-level results in subjects recruited from primary care clinics when compared to a prognostic reference standard.

For secondary efficacy endpoints, the following will be analyzed:

- 1) Sensitivity and specificity of IDx-DR using RV700 based on subject-level results against a Level I Prognostic Reference Standard (PRS)
- 2) Sensitivity and specificity of IDx-DR using the RV700 based on eye-level results when compared to the Wisconsin Fundus Photograph Reading Center Level II Standard grading of the RV700 images

---

**Digital Diagnostics Confidential.** This document is intended for internal use only and may not be disclosed or reproduced in whole, or in part, for external distribution in any form without express written permission of DDx Legal. All hard copies should be checked against the current electronic revision prior to use and destroyed promptly thereafter. All hard copies are considered uncontrolled documents.

- 3) Sensitivity and specificity of IDx-DR using RV700 based on subject-level results when compared to the Wisconsin Fundus Photograph Reading Center Level II Standard grading of the RV700 images
- 4) Percent of total cases where a diagnostic result can be provided by IDx-DR with the RV700
- 5) Positive Predictive Value (PPV) and Negative Predictive Value (NPV) of IDx-DR with the RV700
- 6) Sensitivity and specificity of IDx-DR as if all PRS-determined positive cases with no diagnostic result provided were false negatives and all PRS-determined negative cases with no diagnostic results were false positives, i.e., a “worst case scenario” of the impact of “Exam Quality Insufficient” results.

For the Precision Substudy, the following will be analyzed:

- 1) Eye-level DDx algorithm score mixed model estimates of the operator, camera, sequence, dilation, and replicate effects
- 2) Average Positive Agreement (APA) in intra- and inter- configurations of RV700 cameras/operators
- 3) Average Negative Agreement (ANA) in intra- and inter- configurations of RV700 cameras/operators
- 4) Average Ungradable Agreement (AUA) in intra- and inter- configurations of RV700 cameras/operators
- 5) Overall agreement
- 6) Subject-level DDx algorithm mixed model estimates of the operator, camera, sequence, dilation, and replicate effect.

Section 9 has further details on the primary, secondary, and Precision Substudy endpoint analyses.

## 8.2. Safety Assessments

The proposed study is expected to introduce only minimal risk to both the camera operators and subjects because the RV700 camera is commercially available for ocular fundus photography and Tropicamide 1% eye drops for pupil dilation are an FDA-approved drug product used in standard care and have been demonstrated to have minimal side effects [11].

### 8.2.1. Safety Monitoring

Ongoing safety monitoring will be performed by the CRO on behalf of the Sponsor. The CRO will review reported AEs received from the clinical study sites on a regular basis and report them promptly to the Sponsor. Investigators and the Sponsor will be notified if unreported AEs are observed in study records by the monitors during routine or for cause monitoring activities. The

Sponsor will review, document, and report (if applicable) adverse events (AEs), including Adverse Device Effects (ADEs) or Unanticipated Adverse Device Effects (UADEs), submitted by clinical investigators. Events considered serious and unexpected by the site staff or the CRO will be immediately investigated by the Sponsor to determine if the event qualifies for expedited reporting to regulatory authorities.

### Adverse Event

An adverse event (AE) is defined as any untoward medical occurrence, unintended disease or injury, or untoward clinical signs whether or not related to the investigational medical device. This includes events related to the medical device and events related to the procedures involved.

### Serious Adverse Event

A Serious Adverse Event (SAE) is defined as an AE that:

- Led to death;
- Led to serious deterioration in the health of the subject, users, or other persons as defined by one or more of the following that resulted in:
  - a life-threatening illness or injury, or
  - a permanent impairment of a body structure or a body function, or
  - hospital admission (>24 hours) or prolongation of existing hospitalization, or
  - medical or surgical intervention to prevent permanent life-threatening illness or injury, or permanent impairment to a body structure or a body function;
- Led to fetal distress, fetal death, or a congenital anomaly or birth defect

*Note:* Planned hospitalization for a pre-existing condition, or a procedure required by the protocol, without serious deterioration in health, is not considered a serious adverse event.

The Sponsor will be responsible for coordinating the expedited reporting of serious and unexpected AEs to regulatory authorities within the required timeframes once the determination for reporting has been made.

### **8.2.2. Methods and Timing for Assessing, Recording, and Analyzing Safety Parameters**

Safety will be evaluated during the time the subject is in the study, which will include from the time of consent through the time of exit. Safety will be assessed by frequency and incidence of ADEs and UADEs.

---

**Digital Diagnostics Confidential.** This document is intended for internal use only and may not be disclosed or reproduced in whole, or in part, for external distribution in any form without express written permission of DDx Legal. All hard copies should be checked against the current electronic revision prior to use and destroyed promptly thereafter. All hard copies are considered uncontrolled documents.

Because this is considered a device study, it is consistent to use the following definitions when assessing safety issues:

- **Adverse Device Effect (ADE)**, which means an adverse event related to the use of an investigational medical device.
- **Unanticipated Adverse Device Effect (UADE)**, which means any serious adverse effect on health or safety, or any life-threatening problem or death caused by or associated with its use that had not been previously identified in nature, severity, or degree of incidence.

### **8.2.3. Identification of Events and Timeframe for Reporting**

For the purpose of this study, ADEs and UADEs will only be recorded for the duration of the subject's involvement in the study. Many subjects in this study may have pre-existing medical conditions; however, those pre-existing conditions will not be considered as ADE/UADEs, unless use of the study device elicits a new ADE/UADE or worsens an existing condition in terms of frequency or intensity during or immediately after the use of the study device. All reportable events as defined above, determined to be an ADE/UADE will be recorded in the source documents and entered in the electronic case report form (e-CRF). The Investigator will provide the date of onset and resolution, intensity, frequency, action(s) taken, changes in study device application, relationship to study device, and outcome.

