## 2.3. Benefit/Risk Assessment

The proposed study is expected to introduce only minimal risk to both the camera operators and study subjects. The camera systems being used are commercially available for ocular fundus photography. The Tropicamide 1% eye drops for pupil dilation in this study are approved drug products used in standard practice by ophthalmologists and have demonstrated minimal side effects [11].

The risks associated with using these devices/products in the context of this clinical study are anticipated to be similar to those associated with the use in standard care and are provided below:

- brief discomfort due to light emitted by the fundus camera
- brief discomfort, stinging of the eyes, sensitivity to light, or blurry vision caused by the dilation drops

A serious but rare risk would be an anaphylactic allergic reaction to the Tropicamide 1% eye drops.

As with most diagnostic tools, the principal risks of IDx-DR are those of false positive and false negative results. However, in the context of this clinical study, the IDx-DR results will be masked to operators and treating providers and will not be used to diagnose DR nor guide management or treatment, and therefore do not impact the standard of care or present any increased risk of false positive/negative results.

The benefits associated with using these devices/products in the context of this clinical study are also anticipated to be similar to standard of care along with the addition of the following:

- supporting development of sight saving technologies that may help others with diabetic retinal diseases in the future
- while all subjects enrolled at primary care sites will be referred to ophthalmology according to standard of care, if the prognostic reference standard (PRS) is determined to be mtmDR, the Contract Research Organization (CRO) will notify the study site.

Considering the risk against benefit assessment, it can be concluded that participation in this study may offer benefit with minimal risk compared to the standard of care procedures.

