#### **8.2.6. Guidelines for Determining Causality**

The Investigator will use the following question when assessing causality of an ADE/UADE to study device, where an affirmative answer designates the event as a suspected ADE: Is there a reasonable possibility that the device or its use caused the event? “Reasonable possibility” means that there is evidence to suggest a causal relationship between use of the device and the ADE.

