#### **8.2.8. Anticipated Adverse Device Effects**

Due to the non-invasive nature of the devices, there are no anticipated adverse device effects directly related to IDx-DR or RV700.

The proposed study is expected to introduce only minimal risk to both the camera operators and subjects because the RV700 cameras are commercially available for ocular fundus photography and Tropicamide 1% eye drops for pupil dilation are an approved drug product used in standard care and have been demonstrated to have minimal side effects [11].

The risks associated with using these devices/products in the context of this clinical study are anticipated to be similar to those associated with the use in standard care and are provided below:

- brief discomfort due to light emitted by the fundus cameras
- brief discomfort, stinging of the eyes, sensitivity to light, or blurry vision caused by the dilation drops

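### The AE and SAE sections cover procedure-related events, but the recording, causality and safety-summary rules cover only device effects, so non-serious reactions to the dilation drops have no stated route into the eCRF or the summary

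*Combined protocol and SAP*

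**What the plan says.** The protocol uses two vocabularies for safety.

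The broad one is in 8.2.1. An adverse event is any untoward occurrence whether or not the device is involved, and "This includes events related to the medical device and events related to the procedures involved". The serious adverse event definition in the same section has no device condition. AE evaluation is scheduled for the main study visit (1.2.3) and the substudy visit (1.3.4), and the CRO reviews the AEs that sites report. Section 10 sends SAEs to the sponsor within 3 working days, and to the IRB.

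The narrow one governs what is recorded and summarised:

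- 8.2.2: "Safety will be assessed by frequency and incidence of ADEs and UADEs". An ADE is defined there as an event "which means an adverse event related to the use of an investigational medical device". A UADE must be serious, be linked to use of the device, and be one "that had not been previously identified in nature, severity, or degree of incidence".
- 8.2.3: "All reportable events as defined above, determined to be an ADE/UADE will be recorded in the source documents" and entered in the eCRF.
- 8.2.6: the causality question is "Is there a reasonable possibility that the device or its use caused the event".
- 8.2.7: the 7-day rule for EDC entry applies to ADEs, with a separate rule for UADEs. There is none for other AEs.

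On risk, 2.3 says: "A serious but rare risk would be an anaphylactic allergic reaction to the Tropicamide 1% eye drops". Section 8.2.8 says "there are no anticipated adverse device effects directly related to IDx-DR or RV700", and then lists brief light discomfort and the mild effects of the drops under its heading of anticipated adverse device effects. Anaphylaxis is not in that list.

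**The concern.** The investigational product is IDx-DR paired with the RV700. The dilation drops are not that product, and neither is the camera system used for the 4W and OCT reference imaging. Yet the physical risks that 2.3 expects in this study come from camera light and from the drops, and the only one it calls serious comes from the drops. The safety summary is therefore built on a category that 8.2.8 says is expected to be empty as far as direct effects of IDx-DR or the RV700 go, and no rule assigns drop reactions to it or to any other tabulated category.

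At stake is whether the safety tables can back the statements in 2.3 and 8.2 that the study carries minimal risk. If sites apply the rules differently, the count of mild reactions will depend partly on how each investigator read the word use. The sensitivity and specificity analyses are not affected.

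**Working it through.** No figure in the plan needs reproducing here. The check is to follow three events through the sections as written.

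| Step | A. Non-serious reaction; drops given only for 4W/OCT | B. Non-serious reaction; drops given after failed RV700 attempts, or in the substudy | C. Anaphylaxis meeting the SAE definition |
|---|---|---|---|
| AE under 8.2.1? | Yes, procedure-related | Yes | Yes |
| Elicited at the scheduled AE evaluation? | Yes, if it occurs by then | Same | Same |
| Reported as an SAE (Section 10)? | No | No | Yes, to sponsor within 3 working days, and to IRB |
| Device or its use the cause (8.2.6)? | No, on a plain reading | Arguable | Depends on why the drops were given |
| eCRF/EDC rule (8.2.3, 8.2.7)? | None | Only if judged an ADE | Only if judged an ADE or UADE |
| In the 8.2.2 summary? | No | Only if judged an ADE | Only if judged an ADE or UADE |

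**Event A can arise in ordinary conduct.** Under 7.5, RV700 imaging starts without drops, which follow only after three successive insufficient results. The subject then has dilated 4W imaging on a different camera system. If the RV700 images succeeded undilated, the drops were given for reference imaging alone. An investigator answering 8.2.6 literally would say no.

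**Event B is ambiguous.** In 7.5 this dilation is a step inside the RV700 imaging procedure, and in 7.6 a step inside the IDx-DR exam procedure. Either can fairly be read as use of the device.

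**Event C is reported, but its place in the summary is unclear.** It reaches the sponsor and the IRB as an SAE. Counting it as a UADE requires a link to device use and requires that the effect was not already identified. Section 2.3 names it; the list in 8.2.8 omits it.

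**Section 8.2.8 does not settle A or B.** Its heading suggests that stinging and blurred vision from the drops are device effects. Its first sentence and the ADE definition in 8.2.2 suggest that they are not.

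**Exposure.** Section 4.2 has every substudy subject dilated (36 subjects). For the main study, 1.2 and 7.5 describe dilated reference imaging of each eye, while 4.2 says main-study subjects are dilated only as needed. SAP Section 4 gives a maximum of 282 subjects. The number dilated solely for reference imaging is not stated.

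**The case against.** The best reply is that the protocol does collect these events. It defines AEs broadly, schedules AE evaluation for every subject, has the CRO review reported AEs and pass them promptly to the sponsor, and has monitors flag unreported ones. Section 8.2.12 has AEs followed, and 8.2.4 refers to other events entered in the EDC. Anaphylaxis meeting the SAE definition is reported whatever its relation to the device. Section 8.2.8 puts mild drop effects under anticipated device effects, so a site may well enter them as ADEs. The 8.2.3 field for relationship to the study device would have little purpose if only related events were entered. The drops are an approved product, known allergy is an exclusion, and neither the SAP nor protocol Section 3.1 lists a safety endpoint.

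Most of this stands, and it rules out stronger readings. A reader might infer that all drop reactions, including the named serious one, go unrecorded. The SAE route shows that this is wrong for serious events. A reader might also infer that safety review would miss a cluster of mild reactions; AE review in 8.2.1 and follow-up in 8.2.12 are not limited to device effects, so that does not follow.

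What the reply does not supply is an entry rule or a tabulation rule for non-serious procedure-related AEs. The 8.2.4 text is a closing convention for unresolved events. Scheduled evaluation and CRO review make the sponsor aware of an event, but they do not widen the 8.2.2 summary.

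**Conclusion.** The point holds as an inconsistency with a definite consequence. As written, a non-serious reaction to drops given solely for 4W/OCT imaging is an AE that no stated rule puts in the eCRF or the safety summary. Reactions to drops given to obtain an RV700 result, or in the substudy, may or may not be counted, depending on how a site reads device use. Serious reactions are reported, but their place in the summary and the UADE status of anaphylaxis are not fixed.

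The documents identify which events are affected, not how many. It would be tempting to say that the trial forgoes an upper bound on the reaction rate: with no events in 282 subjects the one-sided 95% bound would be 1 − 0.05^(1/282) = 1.06%. That assumes all 282 are dilated, which the wording of 4.2 puts in doubt, and the trial never set out to estimate this rate. The conclusion does not rest on it.

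The assumption that matters is that sites and data managers follow 8.2.2, 8.2.3, 8.2.6 and 8.2.7 literally. If they enter every reported AE, the eCRF gap closes, but the summary in 8.2.2 is still limited to ADEs and UADEs. This should be corrected; it does not threaten the primary analysis.

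**What to change.** - In 8.2.2, 8.2.3, 8.2.6 and 8.2.7, extend recording, causality assessment, EDC entry and tabulation to AEs related to any study procedure (dilation, RV700 imaging, 4W or OCT imaging) and to all SAEs.
- Add a relatedness field to the eCRF: device, dilation, reference imaging, unrelated.
- Report procedure-related AEs separately from ADEs, so that the device count keeps its meaning.
- Reconcile the two statements in 8.2.8 with each other, and the risk lists in 2.3 and 8.2.8, so that anaphylaxis has one classification for UADE purposes. Which classification is for the sponsor to decide.

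The cost is protocol wording, one eCRF field and possibly a slightly higher reported adverse-event count. AE evaluation is already scheduled at both visits, and no imaging step, dilation rule or sample size changes.

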### **8.2.4. Follow-up of Adverse Device Effects**

ADEs that occur on the day of the visit will be followed up to adequately evaluate the subject's safety or until the event stabilizes. When the event resolves, a resolution date will be documented on the case report form. All UADEs will be followed until resolution or until the subject is medically stable. All other events that cannot be resolved by 30 days after the last study contact will be considered resolved by convention and entered in the Electronic Data Capture (EDC) system.

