#### **8.2.7. Reporting Procedures**

All recordable ADEs will be entered into the EDC within 7 days of identification. Recordable UADEs will be reported within 3 working days of identification by telephone to the Sponsor at [contact] and entered into the EDC as soon as possible thereafter.

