### 8.2.12. Type and Duration of Follow-up of Subjects after ADEs

ADEs/UADEs will be followed until resolved or considered stable. Adverse events will be followed by the Investigator or a qualified member of the study team. The Investigator or a qualified study team member may review the subject's medical record, contact the subject by phone, or contact the subject's primary care physician for follow-up. Subject safety data will be reviewed on an ongoing basis by the Sponsor.

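### Section 8.2.4 closes some unresolved events as resolved at day 30, an outcome that nobody observed

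*Combined protocol and SAP*

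**What the plan says.** Section 8.2.4 of the protocol handles three groups of events in turn.

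- Visit-day ADEs: "ADEs that occur on the day of the visit will be followed up to adequately evaluate" the subject's safety, or until the event stabilizes.
- UADEs: followed to resolution or to medical stability.
- The remainder: "All other events that cannot be resolved by 30 days after the last study contact will be considered resolved by convention", and entered in the EDC.

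Between the first two rules it says: "When the event resolves, a resolution date will be documented on the case report form".

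Three other sections bear on the same record. Section 8.2.3 says that a reportable event "determined to be an ADE/UADE will be recorded in the source documents" and entered in the e-CRF. Its list of items that the investigator must supply includes the resolution date and ends with "relationship to study device, and outcome". Section 8.2.7 sets the timing: "All recordable ADEs will be entered into the EDC within 7 days of identification". Section 8.2.12 states follow-up without a time limit: "ADEs/UADEs will be followed until resolved or considered stable".

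**The concern.** A cut-off for follow-up is ordinary. The difficulty is the status assigned at the cut-off. The rule selects events that have not resolved and then labels them resolved. If the event is known to be continuing, the label is wrong. If its status is unknown, the label has no support. Either way the assigned outcome is the favourable one.

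Outcome is a required data item under Section 8.2.3, and Section 10 (Data Monitoring) has the investigator endorse the subject data in the EDC. Read literally, an investigator could be asked to endorse resolution of an event that he or she knows is still present. Sites must also decide for themselves which events the residual group contains.

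What is at stake is the accuracy of the outcome field for a handful of safety records. No hypothesis test or safety count depends on it.

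**Working it through.** No arithmetic applies. The 30-day limit is a convention, the documents give no event rate, and there is no derived figure to reproduce. The check is to set the rules side by side.

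**1. Condition against label.** The residual rule is triggered by non-resolution at day 30, and its output is a resolved status. The text provides no ongoing, stable or unknown status for these events. An ADE identified by the last contact should already be in the EDC within the 7 days of Section 8.2.7. For that ADE, the day-30 step can add no new event; it can only set the event's status.

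**2. Resolved against stable.** Section 8.2.4 gives UADEs two alternative end states, resolution or medical stability. Section 8.2.12 gives ADEs and UADEs the same two. The protocol therefore treats stable as something other than resolved. The convention merges them: an event that is stable but present at day 30 would be labelled resolved.

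**3. Which events are covered.** The residual group follows a rule for visit-day ADEs and a rule for UADEs.

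| Reading | Events under the convention | Fit with 8.2.12 |
|---|---|---|
| Broad: everything except UADEs | All ADEs that are not UADEs, and possibly unrelated adverse events | Conflicts for an ADE neither resolved nor stable at day 30: 8.2.12 continues follow-up, 8.2.4 closes it. A stable ADE can be closed under both, but as resolved |
| Narrow: everything except UADEs and visit-day ADEs | ADEs arising off the visit day, and possibly unrelated adverse events | Little conflict, because the other two rules of 8.2.4 say much the same as 8.2.12 |

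No other section chooses between these readings. Whether unrelated adverse events are reached at all is also open. Section 8.2.3 ties e-CRF entry to ADEs and UADEs, while Section 8.2.1 has the sponsor document adverse events in general.

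**4. How many events.** Under Section 8.2.3 recording is limited to the subject's time in the study. Sections 1.2.3 and 1.3.4 each schedule one visit, which the synopsis puts at two to three hours for the main study and about five hours for the 36 substudy subjects. Most recordable ADEs would therefore arise on a visit day. On the narrow reading, the convention is left with perhaps an ADE arising between the main visit and a substudy visit, plus any unrelated events that are recorded.

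**5. What depends on the label.** Section 8.2.2 assesses safety by frequency and incidence. Duration and resolution are not analysed. The 3-working-day reporting of UADEs, deaths and serious adverse events in Section 10 does not use the day-30 status, and neither do sensitivity and specificity.

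**The case against.** The strongest reply is that the rule reaches almost nothing. Visits last hours, nearly every ADE will be a visit-day ADE with its own follow-up rule, and UADEs have theirs. Section 8.2.12 already follows ADEs until they resolve or stabilize, so no subject loses protection. This stands, and it is why the point is minor. It does not make the label accurate for the events that remain.

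A second reply is that the documents do not show the EDC outcome codes, any flag for administrative closure, or the CRF completion instructions. This also stands. A reader might infer that the final safety data will be unable to separate observed resolution from closure by convention, or that resolution dates will be invented. The documents do not support either inference. Section 8.2.4 ties the resolution date to actual resolution, so an event closed by convention may simply carry no date, and a flag may exist. What the text does support is narrower: the protocol directs that the event be treated as resolved and provides no other status.

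A reader might also infer that serious but already known reactions escape follow-up, because a UADE must be previously unidentified and Section 2.3 says: "A serious but rare risk would be an anaphylactic allergic reaction to the Tropicamide 1% eye drops". That does not follow. The drops are given at the visit, so such a reaction would be expected on the visit day. If it counts as an ADE, the first rule of 8.2.4 and Section 8.2.12 follow it to stability. If it does not, because the drops are not the investigational device, that is a question about the ADE definition and not about the 30-day rule. If serious, it is still reportable within 3 working days.

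**Conclusion.** The point holds as a minor one. For a residual group of events, at most those that are not UADEs and perhaps only those that are also not visit-day ADEs, Section 8.2.4 assigns a resolved outcome that was not observed. It also blurs the resolved/stable distinction made in the same section and in 8.2.12.

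No count of affected events can be given, because the documents state no event rate. That few are likely rests on the single short visits and on Sections 2.3 and 8.2.8, which describe mostly brief effects. The conclusion takes the text at its natural meaning, that an event considered resolved and entered in the EDC is entered as resolved; the protocol does not spell out the coding. Safety counts, expedited reporting and the accuracy endpoints are unaffected on either reading.

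**What to change.** Replace the last sentence of 8.2.4 with a rule along these lines: ADEs and UADEs are followed until resolved or stable, as in 8.2.12; follow-up of any other recorded event may close administratively 30 days past the last contact; at closure the last-known status is recorded as ongoing, stable, resolved with sequelae, or unknown; and a resolution date is entered only when resolution was observed. This keeps the 30-day close, names the events that it covers and brings the two sections into line.

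The cost is a short edit to one section and an EDC outcome code for last-known status, if the EDC does not already have one. An ADE still unstable at day 30 may need a phone call or record review, which Section 8.2.12 already allows. No analysis, sample size or endpoint changes.
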